#### Secondary outcomes

The secondary endpoints of the study are defined as follows:Intraoperative blood loss in milliliters measured during the overall surgical procedure (from first skin incision to full skin closure)Incidence of CO_2_ embolisms in the right atrioventricular system detected by intraoperative transesophageal echocardiography with a mid-esophageal right ventricular inflow-outflow (RVOT) view before, during, and after the parenchymal transection phase. The occurrence of CO_2_ embolisms will be graded according to the “Tübingen Venous Air Embolism Grading Scale” [15]Other surgery-related secondary endpoints include:The quality of the surgical field (L-SRS)The overall time of surgery and the duration of the parenchymal transection phase in minutesIIP at the end of the parenchymal transection phase and mean IIP outside of the parenchymal transection phase, number of surgeries with an increase of +2 mmHg, +4 mmHg, or +6 mmHg, etc.Occurrence of intraoperative surgical complications other than gas embolismConversion rate to open laparotomyDifficulty of liver resection according to the “scoring system for laparoscopic liver resection”Indocyanine green (ICG) clearance after the parenchymal transection phase and 24 h laterOther anesthesia-related secondary outcomes include:Application of perioperative peridural catheter (drug, dosage, duration)Mean dose of narcotic drugs (propofol, sufentanil, remifentanil, lidocaine, esketamine, rocuronium, cisatracurium, and others)Transfusion rate and coagulation factor administrationNeuromuscular blockade reversal (sugammadex and others)Usage of vasopressors (epinephrine, noradrenaline, dobutamine, theodrenaline-cafedrine, and others)Use of buffer solutions (natrium bicarbonate and tris(hydroxymethyl)aminomethane)Mean EtCO_2_ and occurrence of an abrupt end-tidal carbon dioxide (EtCO_2_) partial pressure decrease ≥5 mmHg and mean arterial carbon dioxide pressure (paCO_2_), pH and bicarbonate at 15-min intervals during the parenchymal transection phase and every 30 min outside of itA sudden decrease in MAP > 20 mmHgAbnormal regional cerebral oxygen saturation (rScO_2_) (defined as a decrease in rScO_2_ > 15% compared with baseline or rScO_2_ < 50%)Mean central venous pressure (CVP) and increased CVP (CVP > 10) at 15-min intervalsPeripheral oxygen saturation (SpO_2_) <90%, or changes in SpO_2_ or hypoxia (SpO_2_ < 90% lasting at least 1 min)Heart rate (HR)Mean arterial pressure (MAP) and hypotension (MAP < 65 mmHg)Arterial lactateVentilation parameters: mean positive end expiratory pressure (PEEP), inspiratory pressure (Pinsp), mean airway pressure (Pmean), breathing ratePerioperative fluid balancePostoperative secondary outcomes include:Surgery-related postoperative complications (e.g., wound impairments, biliary leakage, postoperative liver failure, pulmonary complications)Overall postoperative morbidity within 30 postoperative days measured via the Comprehensive Complication Index (CCI) [16] according to the Clavien-Dindo classification [17]Dose of postoperative opioid analgesics (piritramide and others) and dose of postoperative non-opioid analgesics (metamizole, paracetamol, and others) for 48 h after the surgeryPostoperative laboratory values (e.g., bilirubin, c-reactive protein (CRP), international normalized ratio (INR))Length of the intensive care unit (ICU) stays, readmissions to the ICU, and overall hospital stayNausea and vomiting, use of emetic medications, day of first postoperative bowel movement, use of prokinetic medicationsQuality of recovery based on the Quality of Recovery 40 (QoR-40) questionnaire on postoperative days 1, 3, and 7Histopathology outcomes (e.g., lymph node yield, perineural and lymphovascular invasion)Postoperative neurological recovery according to the National Institutes of Health Stroke Scale (NIHSS)Outcomes assessed during follow-up include:30-day and 90-day survival.Hospital readmission within 30 days of remission.In case of a malignant diagnosis, oncologic outcome (overall survival and disease-free survival) will be evaluated based on [18] surgical margins (R0—no evident tumor along the transection surface or within 1 mm of it; R1—microscopically positive; R2—grossly positive).To assess the effect of pneumoperitoneum pressure on tissue damage:Plasma damage-associated molecular patterns (DAMPs), for example, heat shock protein 70 (HSP70), high mobility group box 1 (HMGB1), nuclear deoxyribonucleic acid (nDNA), and mitochondrial DNA (mtDNA).Plasma cytokines (for example, tumor necrosis factor alpha (TNFα), interleukin-10 (IL-10), and IL-6) will be evaluated from blood samples drawn directly before the parenchymal phase and at the end of it, as well as on postoperative days 1 and 3.In addition, liver and peritoneal biopsies will be taken before and after the parenchymal transection phase of the liver resection. Biopsies will be used to extract mRNA and determine:Levels of hypoxia-inducible factor 1-alpha (HIF1α), TNFα, IL-1β, IL-6, vascular endothelial growth factor (VEGF), hepatocyte growth factor (HGF), and platelet-derived growth factor (PDGF).

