## Statistical methods

### Statistical methods for primary and secondary outcomes {20a}

The data will be managed and analyzed according to the applicable standard operating procedures (SOPs) within the shared unit of the clinical trial center. All relevant study information will be documented in case report forms (CRFs), which will be reviewed by the study team prior to data entry. A safety analysis will be conducted for all patients who underwent one of the interventions. Serious adverse events will be documented immediately, prompting notification of the principal investigator. Absolute and relative frequencies, as well as the severity and relationship to the intervention, will be compared between intervention groups.

The modified intention-to-treat (mITT) analysis will be used to evaluate the primary and secondary endpoints. The mITT set includes all randomized patients who initiated the intervention and met intraoperative inclusion criteria (e.g., exclusion of a PFO). Patients excluded intraoperatively due to contraindications (e.g., adhesions or peritoneal carcinomatosis) will not be included in the analysis.

The primary endpoint (intraoperative blood loss during the parenchymal transection phase) will be analyzed using linear regression if data follow a normal distribution. If normality is not met, a non-parametric bootstrap method will be employed to calculate confidence intervals. The 90% confidence interval (CI) for the mean difference between the two groups will be calculated, and the lower bound of this interval will be compared to the predefined non-inferiority margin of 100 ml to confirm non-inferiority. The corresponding *p* value will also be computed.

Secondary endpoints will also be analyzed:Continuous variables: These will be analyzed using descriptive statistics (mean, standard deviation, quartiles) along with two-sided 95% confidence intervals (CIs).Categorical variables: Absolute and relative frequencies will be reported, and two-sided *p* values will be calculated using the chi-squared test or Fisher’s exact test.

All statistical tests will be two-sided and conducted at a significance level of *α* = 0.05. Analyses will account for stratification to minimize bias and ensure accurate *p* values [22].

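### Continuous secondary endpoints get descriptive statistics and 95% intervals with no between-arm difference named, so the plan does not secure an estimate of the effect of pressure on tissue damage

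*Protocol article*

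**What the plan says.** The section on statistical methods for primary and secondary outcomes {20a} treats three kinds of endpoint differently.

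- **Primary endpoint:** linear regression or a bootstrap, with the target named: "The 90% confidence interval (CI) for the mean difference between the two groups will be calculated".
- **Categorical secondary endpoints:** frequencies with a between-arm test, since two-sided p "values will be calculated using the chi-squared test" or Fisher's exact test.
- **Continuous secondary endpoints:** "These will be analyzed using descriptive statistics (mean, standard deviation, quartiles) along with two-sided 95% confidence intervals (CIs". No difference, model or test is given.

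Two general sentences close the section: "All statistical tests will be two-sided and conducted at a significance level of" 0.05, and "Analyses will account for stratification to minimize bias". The stratifiers, listed under Stratification variables, are centre and conventional versus robot-assisted surgery.

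The Secondary outcomes section introduces the plasma and biopsy markers with the purpose "To assess the effect of pneumoperitoneum pressure on tissue damage". The section on biological specimens {33} likewise says that specimens serve to evaluate different pressures. Plasma cytokines "will be evaluated from blood samples drawn directly before the parenchymal phase and at the end of it", and again on postoperative days 1 and 3. Secondary outcomes and Table 1 both place peritoneal sampling at the start and the end of transection.

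**The concern.** An effect of pressure is a contrast between arms. A mean, SD and quartiles do not estimate it, and an interval does so only if it is an interval for the difference. Two analysts could follow the continuous-endpoint sentence faithfully and report different things: one an interval for each arm's mean, the other an interval for the difference. The first report would leave readers to judge the effect by whether two intervals overlap, which is not a valid test of the difference.

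The endpoints affected include those the abstract puts forward: tissue damage, operation time and duration of hospitalization. For the markers, patients give study biopsies and repeated blood samples, so the estimate those samples are meant to deliver should be fixed in advance. The pre-transection sample is also a natural covariate. It is taken while both arms are planned to be at the same baseline pressure, before the randomised difference begins, yet the analysis section gives it no role.

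**Working it through.** **1. The plan's own sample size.** Inputs from Sample size {14}: margin 100 ml, SD 184 ml, true difference 0, power 80%, α 0.05, ICC 0.05, four centres, 5% loss.

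- With α taken one-sided: n = 2 × (184/100)² × (1.645 + 0.842)² = 41.9, so 42 per group, as stated.
- Design effect with 42/4 = 10.5 patients per centre per arm: 1 + 9.5 × 0.05 = 1.475. Then 42 × 1.475 = 61.95, so 62.
- Loss: 62/0.95 = 65.3, so 66 per group, as stated.

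The figure reproduces and is not in dispute. It provides the 66 per arm used below.

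**2. The two readings of the interval.** The document gives no marker SDs, so results are in SD units (normal approximation, 1:1).

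- Interval for one arm's mean: half-width 1.96/√66 = 0.241 SD.
- Interval for the arm difference: half-width 1.96 × √(2/66) = 0.341 SD.

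Two per-arm intervals overlap until the means differ by 2 × 0.241 = 0.482 SD, although the interval for the difference already excludes zero beyond 0.341 SD. The two readings can therefore lead to different impressions of the same data.

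**3. What the pre-transection value could add.** Let ρ be the correlation between pre- and post-transection values. The document gives no value; 0.3 to 0.7 is assumed. Variances are relative to a post-only comparison: 1 − ρ² with baseline as covariate, 2(1 − ρ) for a change score.

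| ρ | Covariate-adjusted variance | Cut against post-only | Half-width, SD | Equivalent n per arm (66/(1 − ρ²)) | Change-score variance | Cut against change score |
|---|---|---|---|---|---|---|
| 0.3 | 0.91 | 9% | 0.325 | 73 | 1.40 | 35% |
| 0.5 | 0.75 | 25% | 0.295 | 88 | 1.00 | 25% |
| 0.7 | 0.51 | 49% | 0.244 | 129 | 0.60 | 15% |

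The last column is 1 − (1 − ρ²)/(2(1 − ρ)); at 0.7, 1 − 0.51/0.60 = 15%.

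The difference detectable with 80% power is (1.96 + 0.842) × √(2/66) = 0.488 SD from post-only values. Multiplying by √(1 − ρ²) gives 0.465, 0.422 and 0.348 SD at the three correlations.

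**4. Where a baseline exists.** Plasma and peritoneum: Secondary outcomes and Table 1 agree on samples at both ends of transection. Liver: Secondary outcomes has biopsies before and after, Table 1 lists only tissue from the resection specimen, and section {33} speaks of two tissue biopsies from liver and peritoneum, which can be read as one of each. A pre-transection liver value is therefore not secure. Operating time and length of stay have no pre-transection value, so step 3 does not apply to them.

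**The case against.** The strongest reply is that the text is unspecific rather than wrong. A reader might infer that the trial will only describe these endpoints, report no between-arm effect and discard the pre-transection values. The document does not support that. Intervals are planned, and they could be for the difference, as they are for the primary endpoint. The closing sentence on stratification makes most sense for an arm comparison. Nothing says the pre-transection values will be ignored; both time points are in the outcome definition. Whether they enter as a covariate, a change score or part of a repeated-measures model is commonly settled in an analysis plan, which is not shown here.

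Much of this stands. The defect is an unnamed target, not a declared absence of a contrast, and the silence on baseline values is no proof of neglect. The largest precision figure also depends on a post-only comparator that the protocol never specifies.

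The reply does not remove the main point. The section does state a method for these endpoints. It names the contrast for the primary endpoint and tests for the categorical ones, then names neither here. The stratification sentence supplies no estimate.

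**Conclusion.** The point holds in limited form. As written, the method for continuous secondary endpoints does not commit to a between-arm difference, although the tissue-damage aim requires one. This should be corrected. It rests on the wording alone and needs no assumption.

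Baseline adjustment is the weaker half: a worthwhile improvement while the text is being corrected, not a demonstrated error. Its benefit is a 9% to 49% cut in the variance of a marker contrast against a post-only comparison, or about 15% against a change score at a correlation of 0.7. The starting point is an unadjusted half-width of about 0.34 SD at 66 per arm. The correlation range is assumed, and so is complete marker data on all 66; with 62 per arm the unadjusted half-width is 0.352 SD.

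The consequences stay within the secondary endpoints. The primary analysis, the sample size and the non-inferiority conclusion are untouched.

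**What to change.** Replace the sentence on continuous secondary endpoints with wording such as:

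> Continuous secondary endpoints are summarised by arm and compared between arms with a model containing arm, centre and surgical approach; the estimated between-arm difference is reported with its two-sided 95% confidence interval. For plasma DAMPs, plasma cytokines and peritoneal mRNA, the pre-transection value is added as a covariate. Skewed outcomes are analysed on the log scale or by another suitable method.

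Length of stay is likely to need the skewed-outcome provision. The text should also say how the marker samples from days 1 and 3 enter, for instance as separate time points or in one repeated-measures model.

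Reconcile Secondary outcomes, Table 1 and section {33} on whether a liver sample is taken before transection. Extend the covariate to liver mRNA only if the reconciled text confirms one.

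For plasma and peritoneum the cost is analysis wording only, since the samples are already planned. The change should be made before data are analysed by arm. If the analysis plan already names the difference and the covariate, aligning this sentence with it is enough.

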### Eligibility criteria {10}

Inclusion criteria consist of:Age equal or older than 18 years.Capacity of consent.Planned elective conventional laparoscopic or da Vinci-assisted major liver resection or resections near the liver hilum or the hepatic venous vasculature. Major liver resections are defined as the resection of 3 liver segments or more (right and left partial hepatectomies, extended right and left hepatectomies, liver resections of 3 or more segments). Right posterior sectionectomies and mesohepatectomies of ≥2 liver segments are considered resections in proximity to the liver hilum or hepatic venous vasculature.

All study participants must give informed consent before study enrollment.

Exclusion criteria represent:The participation in another trial with interference of intervention of this studyBeing a woman who is pregnant or breast-feeding or planning to become pregnantAmerican Society of Anesthesiologists (AS) score >3Language barrierAny contraindication to a minimally invasive surgical approach or intolerance to pneumoperitoneumA patent foramen ovale (PFO) or any other structural cardiac defect that facilitates paradoxical gas embolismsDiagnosis of neuromuscular disease, heart failure NYHA > class II, or chronic obstructive pulmonary disease (COPD)Being on oral anticoagulation therapy other than aspirin 100 mg daily or any other condition known to increase the risk of bleeding

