### Sample size {14}

The sample size calculation is based on the primary endpoint “intraoperative blood loss during the parenchymal transection phase.” A difference of 100 ml in blood loss is considered clinically relevant, setting the non-inferiority margin at 100. Assuming no difference in mean blood loss between the two groups and using a standard deviation of 184 for blood loss in minimally invasive major liver resection [20], the initial single-center sample size required to achieve 80% power (*β* = 0.2) at *α* = 0.05 was calculated as 42 per group. Adjusting for a multicenter study design with an intra-class correlation coefficient (ICC) of 0.05 across four centers, the required sample size increases to 66 patients per group. Accounting for a 5% loss to follow-up, we plan to include a total of 132 patients across both study arms.

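### The chi-squared and Fisher tests named for categorical endpoints do not use the randomisation strata that the plan says its analyses will account for

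*Protocol article*

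**What the plan says.** The protocol article, under Stratification variables, stratifies randomisation by centre and by conventional laparoscopic versus robot-assisted surgery. Recruitment {15} names four hospitals, so there are up to 4 × 2 = 8 strata.

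Statistical methods {20a} gives frequencies for categorical secondary endpoints and says that two-sided p "values will be calculated using the chi-squared test or" Fisher's exact test. No stratified version is named. The section closes with a general commitment: "Analyses will account for stratification to minimize bias and ensure accurate" p values.

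The primary endpoint, blood loss during transection, "will be analyzed using linear regression if data follow a normal distribution", with a bootstrap otherwise. "The 90% confidence interval (CI) for the mean difference between the two groups will be calculated" and compared with the 100 ml margin. No covariates are listed.

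Eligibility {10} admits a wide range of resections, from extended hepatectomies down to smaller central or posterior ones: "Right posterior sectionectomies and mesohepatectomies of ≥2 liver segments are considered resections in proximity to the liver hilum or hepatic venous vasculature". Resection type is not a stratum. The difficulty score appears among the surgery-related secondary outcomes, without its components or the time of scoring.

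**The concern.** The standard chi-squared and Fisher tests pool all patients into one 2 × 2 table. Stratified randomisation balances the arms within strata, which makes the difference between arms less variable than the pooled formula assumes whenever outcome rates differ between strata. The p values are then too large, and power is lost. The plan gives accurate p values as its reason for accounting for the strata, yet the tests it names cannot do so.

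The endpoints affected include CO2 embolism, the harm that motivates low pressure, and conversion and transfusion rates.

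A second matter is efficiency in the primary analysis. Extent of resection plausibly predicts blood loss. If it is left out of the model, the interval that decides non-inferiority may be wider than it need be.

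**Working it through.** **1. The plan's own figure.** Inputs from Sample size {14}: "setting the non-inferiority margin at 100" (ml); "Assuming no difference in mean blood loss between the two groups and using a standard deviation of 184" (ml); 80% power "at *α* = 0.05 was calculated as 42 per group".

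n per arm = 2 × [184 × (1.645 + 0.842) / 100]² = 41.9, so 42. This reproduces with a one-sided 5% test and matches the 90% interval in {20a}. The 66 per arm reproduces with a design effect of 1 + (42/4 − 1) × 0.05 = 1.475, giving 42 × 1.475 = 61.95, rounded to 62, and 62/0.95 = 65.3, rounded to 66. The point raised here shows no error in the sample size.

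**2. Chi-squared against Cochran-Mantel-Haenszel (CMH).** Illustrative rates are 67.1% and 40.8%, from the earlier trial cited in the Discussion. The conditional odds ratio is (0.408/0.592) / (0.671/0.329) = 0.338. The simulation used 40,000 trials per setting, 66 per arm, and eight strata balanced 1:1, with stratum effects evenly spaced on the log-odds scale. The between-stratum SD is an assumption; the documents give none for embolism. Each cell shows chi-squared / CMH.

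| SD (log-odds) | True size, % | Power, overall rates held at 67.1% v 40.8%, % | Power, odds ratio 0.338 held within strata, % |
|---|---|---|---|
| 0 | 5.3 / 5.2 | 85.8 / 85.9 | 85.8 / 85.9 |
| 0.5 | 4.6 / 5.1 | 86.6 / 88.6 | 82.0 / 84.4 |
| 1.0 | 3.2 / 5.0 | 88.1 / 92.5 | 70.2 / 78.3 |

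With stratum effects drawn at random from a normal distribution instead, chi-squared has size 4.5% (SD 0.5) and 3.4% (SD 1.0). The power losses are then about 2 points at SD 0.5, and 3.6 points (rates held) or 5.8 points (odds ratio held) at SD 1.0.

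So the loss is nil at SD 0, about 2 points at 0.5, and about 4 to 6 points at 1.0. The one larger figure, 8 points, arises with evenly spaced strata and the odds ratio held. In that setting the overall low-pressure rate drifts to 45.9%, so it no longer represents 67.1% versus 40.8%.

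As a guide to a plausible SD: if the blood-loss ICC of 0.05 in {14} also applied to embolism on the log-odds scale (an assumption), the between-centre SD would be √(0.05 × 3.29 / 0.95) = 0.42, before any difference by approach. That is near the lower case.

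**3. Blood-loss interval on the plan's 90% rule.** SE = 184 × √(1 − R²) × √(2/66); half-width = 1.645 × SE; power = Φ(100/SE − 1.645). R² is assumed, centre clustering is ignored, and 66 per arm are taken as analysed.

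| R² | SE, ml | Half-width, ml | Power, % |
|---|---|---|---|
| 0 | 32.03 | 52.7 | 93.0 |
| 0.1 | 30.39 | 50.0 | 95.0 |
| 0.2 | 28.65 | 47.1 | 96.8 |
| 0.3 | 26.80 | 44.1 | 98.2 |

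Here R² is the share explained by all covariates together. The stratification sentence already promises centre and approach, so only the part due to planned resection type would be new.

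**The case against.** The strongest reply is that the stratification sentence qualifies the tests named just before it. CMH is itself a stratified chi-squared test, and an analysis plan that is not shown may say so. These are secondary endpoints without a stated power or confirmatory claim, and the error is conservative. The illustrative rates come from a trial with 93.6% minor resections and a different embolism grading scale. All of this limits the size of the point. What remains is that the text names two tests which, as ordinarily run, do not do what the section promises, and one clause would settle it.

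A reader might infer more, in four ways that the document does not support.

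- That the primary analysis ignores the strata. Linear regression can carry centre and approach, and the general sentence covers it.
- That the categorical tests risk false positives. The size falls below 5%; it does not rise above it.
- That the absence of a covariate list is an error. An article commonly leaves this to the full protocol or analysis plan, and nothing in the text excludes adjustment.
- That the difficulty score is wrongly treated as an outcome, and that any difference between arms must be chance. The article gives neither its components nor when it is scored. Table 1 puts assessment of the surgical procedure on the day of surgery, at the same visit as randomisation. If the score uses findings made after allocation, pressure could affect it, and adjusting for it could bias the non-inferiority comparison.

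**Conclusion.** The mismatch is real but confined to the categorical secondary endpoints. In standard form the named tests ignore centre and approach, contrary to the plan's own statement. They are conservative by an amount that depends wholly on how much the strata differ: none if they do not, and a true size of about 4.6% to 3.3% with about 2 to 6 power points lost for assumed log-odds SDs of 0.5 to 1.0.

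The covariate point is an improvement, not a defect. On the 90% interval that decides the trial, an assumed R² of 0.1 to 0.3 would narrow the half-width by 2.7 to 8.6 ml (52.7 to 50.0 or 44.1). Power without adjustment, with clustering ignored, is already 93.0% against the planned 80%.

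**What to change.** In Statistical methods {20a}, name the CMH test with a stratified risk difference and its confidence interval, stratified by centre × approach, for embolism and the other main categorical endpoints. Keep an exact test for very rare events, and say that it is unstratified if so.

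For blood loss, state the model as arm, centre, approach and planned resection type, the last as recorded before randomisation. If normality fails, bootstrap the same adjusted difference, resampling within strata.

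State when the difficulty score is assigned and from what information. Use it as a covariate, and report it as baseline case mix, only if it rests on information fixed before randomisation. Otherwise leave it out of the model.

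The change is to analysis wording only. The strata are already needed for randomisation and the planned procedure for eligibility. It costs a few degrees of freedom in the regression, and any stratum with patients in only one arm contributes nothing to the stratified test. It should be settled before outcome data are examined by arm.
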